### Spirometry

Spirometry is performed by two qualified research assistants under permanent supervision of a pulmonologist (GW) according to the criteria of the American Thoracic Society (ATS)/European Respiratory Society (ERS) task force for standardization of lung function testing [23,24] using a Vitalograph^® ^2120 (Vitalograph Ltd, Buckingham, England). After a minimum of three acceptable and reproducible FVC manoeuvres, a bronchodilator (500 μg terbutaline) is administered to the subject in preparation for the reversibility test. After 15 minutes, another series of three FVC manoeuvres is performed. All spirometric test results are independently validated by a pulmonologist (GW) and by a specialised lung function laboratory assistant who was not involved in the trial. In case of initial disagreement, consensus is obtained during re-examination.

### Informed consent procedure

Written information about the study is sent to the candidate participant after the telephone interview, along with the informed consent form. The candidate has at least one week time for reflection before spirometry and can contact the researcher or the research assistant (RA) for further information at any time. The informed consent form is signed by the participant in presence of the RA during the visit for baseline spirometry.

The participant information letter gives information about the existence of two intervention groups only. It says that in one group participants receive "care as usual" by their own GP (this is control group 2) and in the other group participants receive treatment from a trained RN. The latter group is in fact a combination of the experimental group (confrontational counselling by RN + nortriptyline) and control group 1 (health education and promotion by RN + nortriptyline). These two groups are identical with regard to the number and duration of counselling sessions and the use of nortriptyline, but differ only concerning the content and style of the behavioural support: confrontational counselling versus health education and promotion. Just this difference in content must not explicitly be mentioned in the participant information letter in order to safeguard the internal validity of the study. We would jeopardize the idea behind early detection of patients with airflow obstruction by means of spirometry if we would speak about "confrontational counselling" or mention the target condition (airflow limitation). Participants must not know that we use results from spirometry as part of one intervention. The design we use is adapted from Zelen's design [25,26] which may be particularly useful when evaluating the full unbiased impact of screening interventions [27].

At the end of the study, after the 12-month follow-up visit, all participants will indeed be fully informed about the real nature of the study. All participants and their corresponding GPs will be informed about the result of the spirometry. If a GP needs the results of spirometry for the regular care of his/her patient before the end of the study, the required information will be provided. This procedure is approved by the medical ethics committee of Maastricht University and Maastricht University Hospital.

### Randomization and planning procedure

All eligible subjects with previously undetected mild to moderate airflow limitation are contacted by telephone a few days after baseline spirometry to be randomised to one of the three intervention groups (apart from those candidates who changed their mind and who are no longer willing to participate in the study). Also at this moment, the results of spirometry are not discussed. The database of the trial incorporates a randomization system of seven participants per block, allowing an unequal group allocation of 3 : 3 : 1; experimental group : control group 1 : control group 2. When eligible subjects are contacted by telephone, the RA randomises the subject by pressing a button on the computer screen. The database then randomly allocates the subject. Neither the primary researcher nor any other person involved in the study can predict or influence which treatment group the next participant will be allocated to.

After randomization, all treatment and follow-up visits are planned for the whole study period. A schedule with all visits is sent to the participant. At the same time, the GP of each participant is sent a letter informing the GP that the participant is taking part in the study.

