### Follow-up visits

Three follow-up visits for all participants are scheduled at day 50 (approximately five weeks after the TQD), day 197 (approximately six months after the TQD), and day 379 (approximately twelve months after the TQD; see also figure 1). The TQD in participants from control group 2 is set at 8 weeks after the day participants were randomized and informed about group allocation. We estimated that this would be sufficient time to schedule a consultation with the GP and to prepare stopping smoking, and that the time lag between day of randomization and TQD would be about the same compared to the experimental group and control group 1 (in the latter groups, we account for a delay between day of randomization and start of treatment). Participants receive a reminder letter including a follow-up questionnaire and a cost-diary seven weeks prior to all three visits. The RA calls every participant one week prior to the visit to confirm the appointment. Minor deviations from the scheduling of follow-up visits will be allowed in order to retain as many participants in the study as possible.

At every follow-up visit, participants hand in their questionnaire and cost-diary. The RA briefly discusses the quit attempt. Urine is collected from every self-reported non-smoker for the analysis of cotinine levels.

During the final follow-up visit, spirometry is repeated in all participants. All spirometric outputs are carefully evaluated by a pulmonologist (GW) and reported to the participant's GP by letter. All participants are asked to consult their GP for information about their lung function and further treatment.

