We expect eligible smokers to have a strong preference to be placed in one of the groups receiving counselling by a RN in combination with smoking cessation medication, because they may find this intervention more effective than care as usual by their own GP. Therefore, we expect a lower compliance in participants from control group 2 and differential lost to follow-up in this group. It should be noted here that the intervention in control group 2 is probably not care as usual for smoking cessation as it appears in primary care. This is because smokers are more or less "referred" from the study team to their GP and are likely to ask for the same smoking cessation medication as participants randomized to the other two groups (nortriptyline).

Blinding of neither participants nor RNs is possible, because we want to assess behavioural interventions. All participants know what kind of counselling they receive, as do the respiratory nurses who provide the counselling. However, analysts assessing the cotinine levels and assistants entering data from questionnaires are blinded for the group allocation of participants.

The primary outcome, 12-month prolonged abstinence from smoking, is estimated from abstinence measures at three time points. This outcome is therefore no perfect measure of continuous outcome, but it is a feasible estimation, which is very usual in this field of research. Abstinence from smoking is the primary endpoint of this study, but can be regarded as a surrogate for the expected long-term positive effects of smoking cessation on health.

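### A constant block of seven at 3:3:1 does not support the statement that nobody involved can predict the next allocation

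*Protocol article*

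**What the plan says.** Under Randomization and planning procedure, the trial database holds "a randomization system of seven participants per block, allowing an unequal group allocation of 3 : 3 : 1". No second block size, random variation of size or concealment of the size is described. Eligible candidates are telephoned a few days after spirometry, and "the RA randomises the subject by pressing a button on the computer screen"; the database then makes the draw. The section closes with the assurance at issue: "Neither the primary researcher nor any other person involved in the study can predict or influence which treatment group the next participant" will enter.

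Other sections bear on who sees the result and who might care about it:

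- Follow-up visits sets the quit date in control group 2 at "8 weeks after the day participants were randomized and informed about group allocation", so the group is disclosed on the day of randomisation.
- Randomization and planning procedure adds: "After randomization, all treatment and follow-up visits are planned for the whole study period".
- The section on the discriminative component gives each treatment group its own nurses. The nortriptyline section has the research assistant count leftover pills at day 50.
- The Discussion lists only the cotinine analysts and the data-entry assistants as blinded. It also says: "We expect eligible smokers to have a strong preference to be placed in one of the groups receiving counselling by a RN".
- Informed consent procedure tells candidates of two options only, nurse care or care from their own GP.

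**The concern.** The assurance is absolute and covers everyone in the study, yet the scheme in the same paragraph contradicts it. When every block has the same known composition, the allocations already made reveal something about those to come, and they fix the last one completely.

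The assistant who triggers the draw very probably learns each result. The article does not say so in words. It follows from disclosure on the same day, separate nurses per arm, the pill count, and the assistant's absence from the list of blinded staff.

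What is at stake is allocation concealment. If the likely next group affected who was randomised when, even without intent, the groups could differ at baseline in motivation to quit. That matters most for control group 2, because candidates are expected to want nurse care and the group is small (a minimum of 32).

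**Working it through.** **Inputs.** Block size 7 and ratio 3:3:1 come from Randomization and planning procedure. Arm sizes come from Sample size calculation: 150 + 150 + at least 32 = 332. If the 3:3:1 ratio is filled to 150:150:50, the total is 350 (an assumption; the article does not state it). The totals only scale the counts; the percentages do not depend on them. The article gives no figure for predictability, so there is none to reproduce.

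**Observer.** The rates below are for a person who knows the block size and ratio and has seen all earlier allocations in the block.

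**Step 1: allocations known with certainty, three arms.** A block has 7!/(3! × 3! × 1!) = 140 equally likely orders. A place is certain when all places left belong to one arm.

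- 7th place: always.
- 6th place: the last two are the same arm, (3 + 3)/21 = 2/7 = 28.6%.
- 5th place: the last three are the same arm, 2/35 = 5.7%.
- Earlier places: never.

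The sum is 1 + 10/35 + 2/35 = 47/35 = 1.343 per block, and 1.343/7 = 19.2%. That is 0.192 × 332, about 64 participants, or about 67 of 350.

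**Step 2: best guess, three arms.** The guesser always names the arm with most places left. Enumerating the 140 orders gives:

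| Place in block | Certain | Best guess right |
|---|---|---|
| 1 | 0% | 42.9% |
| 2 | 0% | 50.0% |
| 3 | 0% | 51.4% |
| 4 | 0% | 55.7% |
| 5 | 5.7% | 60.0% |
| 6 | 28.6% | 64.3% |
| 7 | 100% | 100% |
| Sum per block | 1.343 | 4.243 |

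Accuracy is 4.243/7 = 60.6%. Under simple 3:3:1 randomisation it is 3/7 = 42.9%.

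**Step 3: nurse care versus GP care.** The single control group 2 place is equally likely at each of the seven positions. The mean number of places after it is (6 + 5 + 4 + 3 + 2 + 1 + 0)/7 = 3, so 3/7 = 42.9% of allocations are known not to be control group 2. (This equals the simple-randomisation figure in step 2 by coincidence.)

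The next place is known to *be* control group 2 only when that place comes last: 1/7 of blocks, hence 1/49 = 2.0% of allocations, or about 7 participants.

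Always guessing nurse care is right 6/7 = 85.7% of the time without blocks. With blocks of seven the best guess is right (6 × 6/7 + 1)/7 = 43/49 = 87.8%, a gain of about 2 percentage points.

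**Step 4: effect of varying the block size.** In simulation, a guesser told each block's size finds these shares of certain allocations and of correct best guesses:

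- blocks of 7: 19.2% and 60.6%;
- blocks of 14: 10.7% and 56.4%;
- blocks of 21: 7.4% and 54.2%;
- an equal random mix of the three: 10.4% and 56.0%.

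Concealing the sizes can only lower these, so the last line is an upper bound for the mixed scheme.

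**The case against.** The strongest reply is that prediction needs conditions the article does not show. The guesser must know the block size and follow every allocation. The article does not say whether the assistants knew the size. Two assistants perform spirometry, and how the randomisation calls were shared is not given. This stands: the rates are ceilings, not estimates of what happened.

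Second, the database makes the draw, so nobody can change an allocation. This also stands. Any influence could only be indirect, through who is randomised when.

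Third, a reader might infer that the assistant chooses the order of calls, plans the visits, and can take a withdrawal in the same call once the next group is guessed. The documents do not support this. The article uses the passive for both contacting and planning, says calls come within a few days of spirometry, and notes only that candidates who changed their minds are not randomised, without saying when they do so. Consent is signed earlier, at the spirometry visit.

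Fourth, a reader might take the primary comparison to be compromised. The stated motive does not reach it: candidates are told only of nurse versus GP care, so their preference cannot separate the two nurse arms. For the comparison it does reach, the gain in guessing is small (step 3).

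What survives is the sentence itself. It is unconditional, and for an informed observer the scheme beside it makes it untrue.

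**Conclusion.** The point holds in a limited form. A constant block of seven at 3:3:1 does not ensure that the next allocation is unpredictable. At worst, about one allocation in five is certain and three in seven are known not to be control group 2. The claim that nobody can influence allocation stands as far as the draw itself is concerned.

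The exposure is mainly in the secondary comparison with control group 2, and even there the next place is known to be that group in only about 2% of allocations. The documents give no evidence that selection occurred.

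The conclusion rests on two assumptions: that the block size was known or could be worked out by recruiting staff, and that the assistant saw each result. The second is a strong inference; the first is open. Confidence is medium. The change is worth making because it is cheap and the present wording is wrong.

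**What to change.** 1. Draw block sizes at random from 7, 14 and 21, and conceal the sizes from recruiting staff. Certain allocations fall from 19.2% to at most about 10.4%, and best-guess accuracy from 60.6% to at most about 56%.
2. Let the database allocate only after the candidate's continued willingness has been entered and locked.
3. Correct the closing sentence of Randomization and planning procedure to what the scheme ensures: the database makes the draw, staff cannot alter it, and block sizes vary and are not disclosed to those who recruit. If the fixed block is kept, the article should say who knew its size and should not claim that prediction is impossible.

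The cost is a small change to the existing database and a slightly larger possible imbalance if recruitment stops within a block. In the most extreme order the two nurse arms could then differ by 9 participants in a block of 21, against 3 in a block of seven, with 150 planned per arm.

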### Experimental group and control group 1: L-MIS as the common basis of counselling

Participants from both the experimental group and control group 1 receive counselling delivered by a RN combined with nortriptyline for smoking cessation. The common basis for the counselling is the so-called "L-MIS" protocol for the treatment of nicotine and tobacco addiction which has been implemented among all RNs in the Netherlands in recent years [28].

The number of counselling sessions, their duration and scheduling is fixed in both the experimental group and control group 1 (see also figure 1). The first face-to-face counselling session (FC1; day 1, duration 40 minutes) starts with getting acquainted with each other. The RN tries to build up a relationship with the participant which is based on trust. The participant's smoking characteristics are defined by asking about smoking status, cigarettes smoked per day, and readiness to quit. Nicotine addiction is assessed by number of cigarettes per day and moment of smoking the first cigarette after waking up in the morning. The motivation for quitting smoking is assessed and increased by asking the readiness for quitting and reasons for smoking and quitting. Also, the health risks of smoking are discussed and the pros of quitting. The use of nortriptyline for smoking cessation is discussed, including mechanism, dosage, administration, and possible side effects (for more information about the study medication see paragraph "use of nortriptyline for smoking cessation"). The participant starts with the intake of the study medication the same day.

At the beginning of the second face-to-face counselling session (FC2; day 8, duration 40 minutes), the use of the study medication is evaluated and possible side effects are discussed. Barriers of quitting and the most important problems with previous quit attempts are discussed. The RN tries to increase the participant's self-efficacy towards smoking cessation. The focus of the second session is to prepare the participant for the target quite day (TQD). The RN discusses with the participant how to deal with the most important barriers of quitting smoking. The RN anticipates problems with withdrawal, difficult moments, and craving. The RN provides pointers for the TQD and schedules the telephone counselling on that day.

On the TQD (day 14), the participant is counselled on the telephone (TC; duration 5 – 15 minutes). The RN evaluates the quit attempt, discusses difficult moments, and gives advice for quitting and abstaining from smoking.

The third face-to-face counselling session is scheduled directly after the TQD (FC3; day 15, duration 40 minutes) and starts with an evaluation of the quit attempt and the use of the study medication (including possible side effects). The RN discusses with the participants what is going well and what is problematic with this quit attempt. The RN identifies difficult moments and strategies to deal with theses situations in the future. Participants who did not quit smoking yet or who already relapsed are asked about their reasons and are encouraged to try again.

The fourth face-to-face counselling session (FC4; day 22, duration 40 minutes) basically resembles the third session; the RN evaluates the quit attempt and the use of the study medication. As this is the last counselling session, the focus lies on preparing the participant for continuation of the quit attempt during the follow-up period. The participant is asked to continue with the intake of nortriptyline according to the protocol. At the end of the session, the RN asks the participant's feedback on the perceived effectiveness of the behavioural support and the study medication.

All RNs have had initial training in the use of the L-MIS method and are experienced in the treatment of nicotine addiction. All RNs are trained to use a tailored version of the L-MIS protocol which is specifically designed for this trial. The compliance of RNs with the treatment of participants is stimulated by the use of a protocolized treatment manual, including intervention registration forms providing information per session about all the aspects of smoking cessation counselling to be addressed. The RNs are trained to fill out these intervention forms during each counselling session.

### Discriminative component in the experimental group: confrontational counselling

The number of counselling sessions, the duration, and the scheduling are identical in the experimental group and control group 1. However, specific aspects of "confrontational counselling" are added to the L-MIS in the experimental group which discriminate the treatment from the treatment in control group 1. These aspects derive from the principles of "confrontational counselling" which we have described in more detail elsewhere [29]. Confronting patients with COPD is not an isolated approach but should be integrated into state-of-the-art smoking cessation treatment. Confrontational counselling should consist of several counselling sessions on an individual, face-to-face level, under supervision of a trained smoking cessation specialist, and in combination with evidence-based pharmacological treatment for smoking cessation.

A key element of confrontational counselling is to confront the participant with his/her airflow limitation during the first counselling session (FC1). The RN discusses the results of the participant's individual baseline spirometry and explains the manifestations of COPD; COPD is a slowly progressive, irreversible but treatable disease. Most importantly in this respect is to make the participant understand that his/her cigarette smoking is the primary cause of the disease. The negative effect of smoking on the lungs is illustrated by showing and comparing images of a normal lung and a "smoker's lung". The participant is asked to recognize common symptoms, functional limitations, and participation problems associated with COPD. The natural history of COPD is discussed and illustrated using the so-called "Fletcher curve" (see also figure 2) [30]. Confronting patients with a serious disease that has a bad prognosis arouses fear. Fear arousal is not a goal in itself and it is not likely to automatically lead to the desired action (smoking cessation). Therefore, when discussing the results of spirometry, the RN tries to make the participant understand that there is an effective and feasible therapy for the disease: smoking cessation. Because airflow limitation has been detected early in the participant, early treatment is possible to avoid further damage. Smoking cessation is the only therapy to reduce the progression of the disease resulting in prolonged life expectancy and improved quality of life. The motivation of the participant to stop smoking in combination with the behavioural counselling offered by the RN and the smoking cessation medication (nortriptyline) increases the chance of the participant to quit smoking and to subsequently improve health. At the end of the session, the participant receives a folder with background information on COPD which is developed by the Dutch College of General Practitioners (NHG). In contrast to the experimental group, participants from control group 1 are not being confronted with the detected airflow limitation. The RN from control group 1 is instructed not to discuss the result of spirometry at any time, but to treat the participant as a "healthy smoker".

**Figure 2 F2:**
[figure not shown]
**"Fletcher curve"**. Adapted from Fletcher & Peto (1977): The natural history of chronic airflow obstruction [30].

The information about airflow limitation and COPD during the first counselling session probably has impact on the participant. At the beginning of the second counselling session (FC2), the RN asks the participant to reflect on this information. The RN assesses whether the participant has processed the information correctly and provides feedback on the thoughts, feelings, and beliefs the participant reports. Again, the positive effect of smoking cessation on the history of lung function is stressed and illustrated using the Fletcher curve. This is repeated during later counselling sessions if necessary.

Confrontational counselling comprises more than merely confronting the participant with his/her results from spirometry. It is a patient-centred approach which involves specific communication skills and elements of cognitive therapy. An important condition is a relationship (also known as alliance) between RN and participant in which both roles are equivalent (rather than an expert-recipient relationship). The RN respects the participant's freedom of choice regarding his/her own smoking behaviour. The RN stimulates the participant to reflect on his/her smoking behaviour by carefully listening to the participant's story, using open ended questions, paraphrases, and reflections. Confrontational counselling aims to identify certain cognitions about smoking such as health concerns, risk perception and self-exempting beliefs. The RN tries to challenge irrational beliefs about smoking by raising the smokers consciousness about these beliefs, testing their reality, and by exploring the relationship between beliefs and behaviour. An example for a typical self-exempting belief of a smoker would be: "Smoking is possibly not very harmful because many smokers live long. My grandfather is 85 and he smoked all his life". The RN will try to challenge this belief for instance by conduction an objective risk assessment, or by exploring biases in the belief itself.

At the end of the first, second, and third counselling session, the RN hands out a smoking cessation diary to the participant. Homework is an essential element in cognitive therapy, and self-monitoring diaries are used as extra input for the counselling sessions. In the first diary (evaluated during FC2), participants have to record their smoking behaviour; they have to count the number of cigarettes smoked and have to describe one situation in which they experience great desire to smoke. In the second diary, participants have to record their thoughts when smoking. Again they have to count the number of cigarettes and have to describe one situation, but also what was on their mind directly before and after lighting up. In the third diary (evaluated during FC3), participants have to describe both behaviour and thoughts in situation when they have great desire to smoke.

To ensure the building of an alliance between RN and participant, it is important the participant is counselled by one and the same pulmonary nurse during the whole intervention period to prevent contamination between the groups. Consequently, each treatment group has its own RNs. All RNs have had initial training in the use of the L-MIS method and are experienced in the treatment of nicotine addiction. Additionally, RNs from the intervention group will receive a four-hour group training in confrontational counselling. The group training is lead by a cognitive therapist ([name]) who acts as supervisor throughout the study, and incorporates practical training with a simulation patient. Supervision meetings between RNs and the supervisor will be planned every 6 weeks during the whole intervention period of the trial.

RNs from control group 1 do not receive an introductory group training but receive feedback during regular evaluation meetings between the RN and the principal investigator.

